## Abstract

**Background:**

Feeding is a significant challenge for premature infants in the neonatal intensive care unit (NICU). These patients are often treated with glycerin suppositories to stimulate the passage of meconium and prevent feeding intolerance. Unfortunately, the evidence for this practice is inconclusive.

**Methods/design:**

This protocol is for an external pilot study that will assess the feasibility of a superiority, placebo-controlled, parallel-design, multicenter randomized controlled trial. Participants are premature infants treated in a level 3 NICU with a gestational age 24 to 32 weeks and/or birth weight of 500 to 1500 g. Thirty participants will be recruited as part of this external pilot study. Participants will be randomized to glycerin suppository (250 mg) or placebo starting 48 to 72 h after birth and continuing once daily until meconium evacuation is complete or for a maximum of 12 days. The placebo consists of a 250-mg glycerin suppository placed in the diaper rather than the rectum. Study treatments are administered by the charge nurse on duty who is not otherwise involved in patient care. All other clinicians and research personnel will remain blinded. Outcomes for the pilot study are percentage of eligible participants randomized, percentage of infants reaching full enteral feeds, cost, and treatment-related adverse events (rectal bleeding, rectal perforation, and anal fissure).

**Discussion:**

This external pilot study will assess the feasibility of a multicenter randomized controlled trial of glycerin suppositories in premature infants. The subsequent multicenter trial will have sufficient power to determine whether this treatment strategy is associated with decreased time to full enteral feeds.

**Trial registration:**

ClinicalTrials.gov: NCT02153606

## Background

Feeding is a significant challenge for premature infants in the neonatal intensive care unit (NICU) [1, 2]. These babies have immature digestive tracts and can develop a life-threatening bowel infection called necrotizing enterocolitis (NEC) [3, 4]. Treatment of this condition may require surgery and is associated with substantial morbidity and mortality. This includes short bowel syndrome, dependence on parenteral nutrition, and/or need for additional surgery [5, 6].

Infants who do not develop NEC can still have issues with feeding and growth. Most are supported with intravenous nutrition while enteral feeds are advanced over a period of 1 to 3 weeks. This process can be delayed if infants develop feeding intolerance, characterized by abdominal distension, undigested feeds in the stomach, and decreased bowel movements [7]. This can lead to increased reliance on intravenous nutrition, which is associated with sepsis, extrauterine growth restriction, and poor neurodevelopmental outcomes [1, 2, 8].

Glycerin suppositories are commonly used in premature infants to stimulate the passage of meconium and improve feeding tolerance [9]. This practice is based on the observation that preterm infants experience significant delays in the passage of meconium, which is more viscous than normal stool [10, 11]. Delays in meconium evacuation appear to be associated with a delay in the transition to enteral feeding [12]. Thus, if meconium evacuation could be expedited through the use of glycerin suppositories, this may lead to faster transition to enteral feeding, decreased reliance on intravenous nutrition, and better outcomes. Unfortunately, there is little evidence to support this practice [9–17].

We recently conducted a systematic review on the use of glycerin suppositories and enemas in premature infants [17]. We identified a total of 185 infants from three single-center, randomized controlled trials [14–16]. These studies focused on the prophylactic use of glycerin suppositories (two trials) or enemas (one trial). Across all three trials, there were no differences in terms of meconium evacuation, transition to full enteral feeding, or mortality. There were no reports of rectal bleeding or perforation, but meta-analyzed data revealed a non-significant trend towards increased risk of NEC with active treatment. We concluded that going trials should be carefully monitored and stopped if it becomes clear that this trend is a real effect and not just a spurious correlation.

The results of our systematic review were complicated by the fact that all three trials were underpowered and affected by one or more major methodological issues. As a result, the quality of evidence was low to very low. We concluded that the evidence for the use of glycerin suppositories or enemas in premature infants is inconclusive and that further research is required. As a result, we designed an external pilot study to assess the feasibility of a multicenter randomized controlled trial of prophylactic glycerin suppositories in premature infants.

## Methods/design

### Study design and objective

The glycerin suppositories used prophylactically in premature infants (SUPP) trial is an external pilot study for a superiority, placebo-controlled, parallel-design, multicenter randomized controlled trial [18]. The purpose of the multicenter trial is to determine whether glycerin suppositories decrease the time to full enteral feeding in premature infants. We hypothesize that the multicenter trial will demonstrate that using glycerin suppositories in premature infants results in earlier completion of meconium evacuation. Whether this treatment strategy results in earlier full enteral feeding or improvements in other outcomes remains unclear [17].

The study protocol described here is for an external pilot study to assess the feasibility of a multicenter randomized controlled trial [19, 20]. This includes assessments of cost, recruitment, protocol violations, post-randomization exclusions, and treatment-related adverse events. The pilot will also allow us to determine if modifications to the inclusion or exclusions criteria or duration of study treatments might be required in the multicenter trial.

### Setting

Premature infants will be recruited from the level 3 NICU at McMaster Children’s Hospital in Hamilton, Ontario, Canada. This unit treats almost 1000 infants per year of which approximately 150 would be eligible for our trial.

### Participants

The participants will be premature infants 24 to 32 weeks and/or birth weight 500 to 1500 g (Table 1). Exclusion criteria include the following: congenital gastrointestinal anomalies, surgery within 48 h of birth; culture-proven sepsis, vasopressors, nitric oxide, prostaglandins, suspected coagulopathy (bleeding from any orifice), confirmed coagulopathy (international normalized ratio >1.4, partial thromboplastin time >39 s, fibrinogen <1.00 g/L, platelet count <100 × 109/L), neutropenia (absolute neutrophil count <0.5 × 10^9^/L), and complete meconium evacuation within 48 h after birth.

**Table 1 Tab1:** Participant inclusion and exclusion criteria

Criteria	Definition
Inclusion (any of the following)	
Gestational age	24–32 weeks gestation
Birth weight	500–1500 g
Exclusion (any of the following)	
Congenital gastrointestinal anomalies	Any congenital gastrointestinal anomalies
Clinically unwell	Major surgery within 48 h of birth
	Culture-proven sepsis
	Vasopressors
	Nitric oxide
	Prostaglandins
Suspected coagulopathy	Bleeding from any orifice
Confirmed coagulopathy	International normalized ratio >1.4
	Partial thromboplastin time >39 s
	Fibrinogen <1.00 g/L
	Platelet count <100 × 10^9^/L
Neutropenia	Absolute neutrophil count <0.5 × 10^9^/L
Complete meconium evacuation	2 bowel movements with no meconium

### Interventions

Participants randomized to active treatment will receive a 250-mg glycerin suppository once daily starting 48 to 72 hours after birth (i.e., on day 3 of life). This smaller suppository will be created by cutting the tip off of a 1440 mg glycerin suppository. In order to maintain consistent dosing, we created a plastic measurement guide that results in a 250-mg suppository (Fig. 1). This “tip” will be covered with a water-based lubricant and placed in the infant’s rectum.

**Fig. 1 Fig1:**
[figure not shown]
Plastic measurement guide to ensure consistent dose of glycerin suppositories

Participants in the control group will receive placebo suppositories. In usual practice, partially dissolved suppositories are often ejected from the rectum either with or without stool. In our trial, leaving a suppository in the diaper (but not in the rectum) makes it ambiguous as to whether it was placed in the rectum and ejected or simply placed in the diaper. This approach also ensures that treatment will appear to have been administered to all infants, even if they happen to be in the control group.

Following administration of either treatment, the gluteal buttocks will be held together for 30 s to minimize the likelihood of the suppository being ejected from the rectum. Participants in the each treatment group will receive study treatments once daily until they pass two normal bowel movements free of meconium staining. A similar duration of treatment was used in the randomized controlled trial of glycerin enemas from Austria [14]. Maximum treatment duration will be 12 days (i.e., all treatments will stop on day 14 of life).

All study interventions will be administered by one of the NICU charge nurses on duty. These individuals have years of experience working in the NICU but are not involved in the care of individual patients. All participants will receive a medical order of “nil per rectum” during the period of study treatments. This will be removed once study treatments stop. Study participants will be eligible for rescue glycerin suppository therapy if they are judged by the medical team to have feeding intolerance.

### Randomization

Infants will be allocated to treatment groups via web-based stratified blocked randomization. Previous studies have shown that the size of the infant is highly predictive of the time to full enteral feeds [13]. In order to maintain prognostic balance, participants will be stratified by gestational age: (1) 24–27 weeks 6 days; or (2) 28–31 weeks 6 days. This strategy has been used in other randomized controlled trials of feeding intolerance in premature infants [14, 15, 21, 22]. See Fig. 2 for an overview of the external pilot study.

**Fig. 2 Fig2:**
[figure not shown]
Overview of glycerin suppositories used prophylactically in premature infants (SUPP) trial

Sequence generation will be created using random number software by an unblinded research assistant not otherwise involved in the SUPP Trial. Block size will range from four to six to ensure that there are an equal number of participants in the treatment and control groups. Randomization of study participants will be completed online by a blinded research assistant immediately prior to the administration of the first study treatment. This web-based system will be created using Research Electronic Data Capture (REDCap) software [23]. For each participant, REDCap will assign a three-digit treatment code that will be recorded by the blinded research assistant on the infant’s bedside chart. The charge nurse will use a coding sheet to link the three-digit number for each participant with either active treatment or placebo.

### Blinding

The principal investigator, co-investigators, parents or guardians, physicians, bedside nurses, allied health professionals (e.g., dieticians), research assistants, outcome assessors, and statistical analysts will be blinded to treatment allocation. The only groups who will be unblinded are the participants (i.e., the premature infants who cannot communicate) and the charge nurses responsible for administering study treatments. Adequate blinding of medical staff, bedside nurses, and allied health professionals is essential since these clinicians typically make decisions about advancing or holding feeds during daily patient rounds. If these individuals are aware which treatment the participant is receiving, there is a chance that this knowledge will affect their decision-making and bias the results.

We will employ several strategies to maintain blinding. First, participants in the control group will receive suppositories placed in the diaper rather than no intervention at all. Second, all study treatments will be administered when the participant’s crib is covered. This will ensure that only the charge nurse administering the treatment knows which intervention is given. Third, we have held multiple meetings with the NICU nursing staff prior to the start of the trial to discuss the purpose of blinding and ensure that we have adequate buy-in from these individuals.

### Duration of treatment

Infants enrolled in this trial will receive active treatment or placebo once daily until meconium evacuation is complete. This will be defined as two bowel movements free of meconium staining. Previous studies have demonstrated that this process takes approximately 6 to 9 days [14]. The study intervention will be withheld and reassessed daily in cases of thrombocytopenia (platelet count < 100 × 10^9^/L), suspected coagulopathy (bleeding from any orifice, confirmed coagulopathy (international normalized ratio >1.4, partial thromboplastin time >39 s, fibrinogen <1.00 g/L, thrombocytopenia (platelet count <100 × 10^9^/L), or neutropenia (absolute neutrophil count <0.5×10^9^/L).

The study intervention will be stopped early in cases of clinical deterioration (vasopressors, prostaglandins, culture-proven sepsis, NEC, or death) or treatment-related adverse events (rectal bleeding, rectal perforation, or anal fissure). Previous trials of glycerin suppositories and enemas did not report single case of rectal bleeding, rectal perforation, or anal fissure [14–16]. As such, the risk of these events occurring in the current study is low.

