### Outcomes

Outcomes for the external pilot study will be recruitment rate (i.e., percentage of eligible infants randomized), completion rate (i.e., percentage of infants reaching the primary endpoint of full enteral feeds), and treatment-related adverse events (i.e., safety outcomes). The pilot study will also allow us to better estimate the explicit cost per infant of conducting a randomized trial on this topic (i.e., considering the total costs of database design, data storage, printed materials, and salary for research assistants). We will also assess the frequency and type of protocol violations and post-randomization exclusions.

The primary outcome for the multicenter trial will be time in days to full enteral feeding (defined as 150 mL/kg/day). Advancing the rate of enteral feeds is typically based on a standardized NICU feeding protocol [24–26]. Deviations from this protocol occur when infants become unwell, develop signs of feeding intolerance, or if there are other clinical concerns. Secondary outcomes will include feeding volume on day 14 of life (in mL/kg), days to complete meconium evacuation, days of parenteral nutrition, incidence of NEC, incidence of line sepsis, compliance with treatment regimen, and mortality.

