### Potential pitfalls

Adherence to the study protocol was a serious issue in a randomized controlled trial of glycerin enemas from Austria [14]. This may have occurred because some clinicians did not believe in the efficacy of glycerin enemas and tended to withhold this intervention among participants in the therapeutic arm. This will be less of an issue in our trial since glycerin suppositories are commonly used in the NICU at McMaster Children’s Hospital and are much less invasive.

Another issue to consider is post-randomization withdrawals or exclusions. While this is an issue in any randomized controlled trial, this will present a unique challenge in our study since participants will have been alive for less than 48 h when they are enrolled. Some infants may not have had prenatal screening and serious congenital anomalies that would have excluded them from the study may not be diagnosed until days or weeks after randomization. Even in cases of excellent prenatal care, some conditions (e.g., Hirschsprung’s disease) cannot be diagnosed until the postnatal period [30, 31]. The best way to handle this will be to follow all randomized participants to the primary endpoint of full enteral feeds and analyze the data on the basis of intention-to-treat.

Losing participants to follow-up is unlikely to occur since all premature infants are monitored in hospital until they are tolerating full enteral feeds and reach 37 weeks corrected gestational age. Some participants who are doing well clinically may be transferred to a NICU in a community hospital that is not part of this study, but this is unlikely to occur until after these infants have reached full enteral feeds. Finally, the mortality rate in this population is approximately 10 % [32, 33]. While our exclusion criteria will exclude most of the infants at risk for postnatal mortality, some participants may die before they are randomized, complete the treatment regimen, or reach full enteral feeds.

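### Nitric oxide bars entry but is missing from the on-treatment stop list, which carries over every other ongoing Clinically unwell exclusion

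*Protocol article*

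**What the plan says.** Three parts of the Protocol article bear on this.

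- **Entry.** Participants lists among the exclusions "culture-proven sepsis, vasopressors, nitric oxide, prostaglandins". Table 1 places these four, together with major surgery within 48 h of birth, in one block labelled Clinically unwell.
- **Dosing rule.** Duration of treatment sets the default: "Infants enrolled in this trial will receive active treatment or placebo once daily until meconium evacuation is complete". Interventions sets the limit: "Maximum treatment duration will be 12 days (i.e., all treatments will stop on day 14 of life").
- **Departures from the default.** Duration of treatment gives two. Dosing is withheld and reassessed daily for low platelets, suspected or confirmed coagulopathy, or neutropenia. It is stopped for treatment-related adverse events (rectal bleeding, rectal perforation, anal fissure) or for deterioration: "The study intervention will be stopped early in cases of clinical deterioration (vasopressors, prostaglandins, culture-proven sepsis, NEC, or death").

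Nitric oxide appears only among the entry exclusions.

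**The concern.** The protocol treats nitric oxide at entry as a sign that an infant is too unwell to be given the study treatment. Once dosing has begun, the text has no rule for the same event, while the neighbouring conditions in the same block of Table 1 end treatment.

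The written rule matters more than usual in this trial. Under Interventions, each dose is given by a charge nurse who is not caring for that infant. Under Blinding, the treating team does not know the allocation. The nurse giving the dose therefore leans on the printed criteria, and under those criteria an infant who starts nitric oxide is still due a dose the next day. Protocol violations are also counted as a pilot outcome. On the printed text, stopping for nitric oxide would be the departure and continuing would not.

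**Working it through.** There is no figure to reproduce. The check sets each exclusion in Table 1 beside the on-treatment rules in Duration of treatment.

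| Exclusion in Table 1 | Rule once dosing has begun |
|---|---|
| Major surgery within 48 h of birth | Not applicable: window closed before the first dose at 48 to 72 h |
| Culture-proven sepsis | Stop |
| Vasopressors | Stop |
| **Nitric oxide** | **None** |
| Prostaglandins | Stop |
| Bleeding from any orifice | Withhold, reassess daily |
| INR >1.4, PTT >39 s, fibrinogen <1.00 g/L, platelets <100 × 10^9/L | Withhold, reassess daily (same cut-offs) |
| Neutrophils <0.5 × 10^9/L | Withhold, reassess daily (same cut-off) |
| Complete meconium evacuation | Normal end of dosing |
| Congenital gastrointestinal anomaly | No dosing sentence; late diagnosis is discussed under Potential pitfalls |

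1. Clinically unwell rows: 5. Rows that can newly apply during dosing: 5 − 1 = 4.
2. Of these 4, stop reasons: 3. Remaining: 4 − 3 = 1, nitric oxide.
3. The withhold list is entirely haematological and the adverse-event limb is entirely anorectal, so neither catches nitric oxide. Interventions, Follow-up, Potential pitfalls and Ethical and safety considerations contain no other dosing rule that does.
4. Window in which the gap can operate: day 3 to day 14 of life, 14 − 3 + 1 = 12 days, which agrees with the stated maximum. It closes earlier once meconium evacuation is complete.
5. Infants in whom it means rectal dosing: the active arm, 15 of the 30 planned. Controls have the suppository left in the diaper.

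**The case against.** Entry criteria and discontinuation criteria do different jobs, and nothing in the article says they must match. They already differ: the haematological exclusions become only a temporary hold, and NEC is a stop reason without being an exclusion. The document names no hazard specific to a suppository during nitric oxide. The parenthesis after clinical deterioration could be read as illustrative, so a clinician might stop anyway. A word may also have been lost in condensing the full protocol.

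Part of this stands. The harm is inferred from the protocol's own classification of nitric oxide and is not demonstrated, and a clinician may well step in. That is why the point is minor. It does not remove the mismatch. This protocol chose to mirror its exclusions: the laboratory cut-offs are repeated exactly and the three neighbouring conditions all carry over. One unexplained gap in that pattern looks like a slip. The article prints both lists, so this is not simply detail left to a fuller document, and the stop list carries no wording that marks it as examples.

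A reader might infer a second gap, for congenital anomalies recognised late. The documents do not support making that a finding. Potential pitfalls foresees that "serious congenital anomalies that would have excluded them from the study may not be diagnosed until days or weeks after randomization", treats them as post-randomization withdrawals or exclusions, and provides for follow-up and intention-to-treat analysis. Outcomes adds: "We will also assess the frequency and type of protocol violations and post-randomization exclusions". Only a dosing instruction is unstated, and the full protocol can be expected to hold it.

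**Conclusion.** The point holds for nitric oxide alone, as a minor matter of safety and consistency. Followed as written, an active-arm infant who starts nitric oxide within the dosing window continues daily rectal suppositories in a state that would have barred entry, and the article does not say why.

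This rests on two assumptions: that the stop list is meant to be complete, and that the omission was not deliberate.

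The size cannot be put as a risk, because the document gives no incidence of nitric oxide use after day 3. Two figures are tempting and should not be used that way. One in four (25%) is only a count of list items. The arithmetic ceiling of 14 − 3 = 11 further doses needs nitric oxide to start just after the first dose, evacuation to remain incomplete through day 14, and no other stop or hold. Duration of treatment itself puts evacuation at roughly 6 to 9 days, so 11 is an extreme and not an expected exposure.

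No estimate, error rate, sample size or feasibility analysis is affected.

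**What to change.** In Duration of treatment, add nitric oxide to the clinical-deterioration list, so that it covers vasopressors, nitric oxide, prostaglandins, culture-proven sepsis, NEC and death. Apply it identically in both arms. Keep every randomized infant in follow-up and in the intention-to-treat analysis, as Potential pitfalls already provides. If the omission was intended, one sentence giving the reason would do instead.

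The cost is two words and slightly fewer study doses in infants who start nitric oxide. It needs no new data, staff or visits. Trial status reports that pilot recruitment was already under way, so the change may come too late for some pilot infants. It is still worth making, because the Discussion intends a similar protocol for the multicenter trial if few changes are needed, and the gap would otherwise carry over.
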